#### Missing Data

The trial data set comprises multiple outcome assessments made for each subject over a 72-month period. Therefore, because of the longitudinal nature of the data and the lengthy follow-up period, it is likely that missing outcome data will be present because of loss to follow-up. Patterns and degrees of missingness will be summarized and will inform the approach taken to deal with missing data (eg, missing at random analysis).

#### Association Modeling

Our primary outcome is treatment response status according to NEDA 3. We will perform parametric statistical analysis to determine whether any clinical parameters are associated with outcome—the dependent variable. Multiple repeated measurements of the same individual will be obtained. Therefore, we will apply generalized linear mixed models for binary outcomes, with random effects for time points to account for within-subject correlations and clustering. Clinical factors included in the primary analysis will be EDSS, MRI, and relapse rate measures regressed at baseline. Confounding factors (age, sex, disease duration, etc) will be included as required. By carefully defining covariate values in terms of lagged or leading indicators of study factors, longitudinal data will help us to establish the direction of causation and any lags involved. We will also use Mendelian randomization techniques to help dissect causation from the correlation of evidence for causality. In this analysis, all predictor biomarker variables will be modeled individually and yield a test-specific (unadjusted) *P* value. However, we will apply a Benjamini-Hochberg false discovery rate to adjust the raw *P* value for multiple testing while maintaining power. The secondary outcome variables will be modeled similarly using mixed models with specific parameters dependent on the type of data.

To identify multi-biomarker signatures that predict response in this patient cohort, we will also use machine learning algorithms on the patient cohort data set. Specifically, elastic-net regularized generalized linear model analyses using logistic, linear, or multinomial or Poisson models (depending on the outcome variable) will be conducted within a cross-validation routine to avoid overfitting. This will be performed on the entire factor set using the GLMNet package in the R program [46]. Briefly, GLMNet fits a generalized linear model via penalized maximum likelihood and is akin to a stepwise forward regression with the added feature of being able to perform internal cross-validation. GLMNet allows for both binary and multinomial outcomes. GLMNet allows for the rapid discovery of reduced factor panels that are likely to be associated with outcomes. This complementary approach is not susceptible to multiple testing burdens and will facilitate the identification of the best fitting multifactor signature that is predictive of treatment response [46].

The first analysis time point will be the 6-month assessment, which will be analyzed at this stage. The full data set up to and including the 6-month assessment will be subject to appropriate data cleaning for all variables involved in the primary analysis, consisting of postentry validation checks, and assessing the data for outliers.

Additional interim analysis will be completed at 24 months, 48 months, and again at study termination when all data have been collected.

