## Methods

### Study Design

This study is a multicenter, 6-year, phase IV, low interventional trial. Enrollment of 150 patients with MS was planned across 9 specialist MS clinics in Australia. The Therapeutic Goods Australia approved a cumulative dose of cladribine (10 mg) tablets as 3.5 mg/kg body weight over 2 years administered as 1 treatment course of 1.75 mg/kg per year. After 3 years, patients with MS in consultation with their health care provider will discuss the option of redosing with cladribine tablets, if clinically indicated (by relapse or new MRI activity), switch to another DMT, or continue without change (without commencement of any DMT). For those who will be continued on cladribine, additional courses will be administered as per the previous dosing of 1.75 mg/kg per year.

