### End Points

The primary end point for all outcome measures is the proportion of patients with MS achieving NEDA status (responders) at 6-years relative to screening. However, preliminary end points will also be considered at each of the major biomarker collection points (months 7, 24, 48, and Tv).

The key outcome measures will be NEDA 3 or 4 responders after 6-years. Additional outcome measures will change over time from baseline in MRI parameters (brain volume loss, lesion load, and lesion volume), cognition, lymphocyte subsets, sNfL, and global DNA methylation profiles. In addition, the Tv time point will be used to determine if there are any changes in biomarker status that may predict disease activity. This will be compared with the time point at which the patient is deemed to have stable disease.

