### Statistical Methods

#### Sample Size Calculation

This is a longitudinal study of 150 patients with MS entering the study and predicted to have no more than 20% dropout. Over the study period, we expected 120 patients with MS with longitudinal data for all measured factors: clinical, cellular, and omics. On the basis of CLARITY and CLARITY extension study data, we expect approximately 50% of patients with MS (n=60) to exhibit disease activity according to NEDA 3 (ie, nonresponders) [7-10].

We performed a detailed simulation analysis to assess the power of our sample sizes to detect significant associations at a range of effect sizes and for a range of significance thresholds as per the recommendations of Tsai and Bell [45]. With 120 cases (60 responders vs 60 nonresponders), this study will have 80% power to detect a minimum mean biomarker difference of 10% at a Benjamini-Hochberg false discovery rate of 0.05, which will reasonably balance type I and type II errors. To detect more minor differences, we will use a penalized regression analysis within a machine learning framework using the GLMNet tool [46]. This method is designed for studies with large numbers of predictors and will further enhance the power to identify multi-marker signatures that are predictive of patient response (see details below in the *Association Modeling* section).

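### As written, the mixed model's random effects belong to time points and not to patients; if NEDA status is stacked over visits, P values for baseline predictors are too small

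*Protocol article*

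**What the plan says.** All references are to the protocol article.

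- *Association Modeling* takes NEDA 3 response as the dependent variable. It notes that individuals are measured repeatedly and concludes: "we will apply generalized linear mixed models for binary outcomes, with random effects for time points to account for within-subject correlations and clustering". The clinical factors in this analysis (EDSS, MRI and relapse rate) enter as baseline values. Each biomarker is tested in its own model and the raw P values go into a Benjamini-Hochberg procedure. Secondary outcomes are to be modelled in a similar way.
- *End Points* defines the primary end point as the proportion of patients "achieving NEDA status (responders) at 6-years relative to screening", which is one status per patient. It adds preliminary evaluations at months 7, 24 and 48 and at the variable time point.
- *Sample Size Calculation* states "we expected 120 patients with MS with longitudinal data for all measured factors" and "we expect approximately 50% of patients with MS (n=60) to exhibit disease activity according to NEDA 3".

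The article names no patient-level random effect, within-patient covariance structure or patient-clustered variance.

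**The concern.** The index of a random effect decides which records are treated as correlated. An effect shared by all records at month 24 makes patients at month 24 resemble one another. It says nothing about whether one patient's month-24 and month-48 records go together. Modelling that requires a term indexed by patient.

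A predictor fixed at baseline takes the same value on every record of a patient. A model that ignores the patient therefore treats 120 patients with 4 records each as if they were 480 independent observations of that predictor. The standard error is then too small and the P value too optimistic. Benjamini-Hochberg takes the P values as given, so it carries the error forward.

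The primary outcome makes dependence strong. NEDA measured from screening, once lost, cannot be regained, so every record after first loss is already determined. The associations at stake are meant to inform treatment decisions such as redosing or changing therapy (*Introduction, Overview*).

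**Working it through.** **The plan's own figures.** 150 × (1 − 0.20) = 120, and half of 120 is 60, so the numbers of patients reproduce. The stated "80% power to detect a minimum mean biomarker difference of 10% at a Benjamini-Hochberg false discovery rate of 0.05" cannot be checked, because neither a standard deviation nor a number of tests is given. It also concerns a two-group comparison of means, not the mixed model. The article gives no operating characteristic for the mixed model.

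**Inputs**
- From the article: 120 patients, about 50% NEDA loss by the end of the study, predictors fixed at baseline, random effects for time points only.
- Assumed, because not given: the number of NEDA records per patient, m = 4 (months 7, 24, 48, 72) or m = 6 (yearly); a within-patient correlation (ICC) of 0.1 to 0.7; and, for irreversible NEDA loss, a constant hazard.

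**Step 1: general range.** For a predictor constant within patient, ignoring the patient understates the variance by DE = 1 + (m − 1) × ICC. The true error at nominal 5% is 2 × [1 − Φ(1.96/√DE)].

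| m | ICC | DE | Model SE / true SE | True type I error |
|---|---|---|---|---|
| 4 | 0.1 | 1.3 | 0.88 | 0.086 |
| 4 | 0.3 | 1.9 | 0.73 | 0.155 |
| 4 | 0.5 | 2.5 | 0.63 | 0.215 |
| 4 | 0.7 | 3.1 | 0.57 | 0.266 |
| 6 | 0.1 | 1.5 | 0.82 | 0.110 |
| 6 | 0.3 | 2.5 | 0.63 | 0.215 |
| 6 | 0.5 | 3.5 | 0.53 | 0.295 |
| 6 | 0.7 | 4.5 | 0.47 | 0.356 |

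**Step 2: NEDA that cannot be regained.** Here the correlation follows from the outcome itself. Let S(t) be the probability of still having NEDA at month t. The variance at one visit is S(t)[1 − S(t)], and the covariance of visits s < t is S(t)[1 − S(s)]. With S(t) = 0.5^(t/72):
- S at months 7, 24, 48, 72 = 0.935, 0.794, 0.630, 0.500.
- Sum of variances = 0.061 + 0.164 + 0.233 + 0.250 = 0.708.
- Sum of covariances = 0.052 + 0.041 + 0.033 + 0.130 + 0.103 + 0.185 ≈ 0.544.
- DE = (0.708 + 2 × 0.544)/0.708 ≈ 2.54.
- True error = 2 × [1 − Φ(1.96/1.59)] ≈ 0.22.

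Six yearly records under the same assumptions give DE ≈ 4.26 and a true error of about 0.34.

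**Step 3: simulation, 120 patients, null baseline covariate**
- Outcome that can recover, fitted with a random intercept per time point only and then with a random intercept per patient plus fixed time (300 replicates per setting). For m = 4 and latent ICC 0.23, 0.50 and 0.69, rejection was 0.14, 0.23 and 0.19 with the time-point term, against 0.06, 0.08 and 0.06 with the patient term. For m = 6 and ICC 0.23 it was 0.13 against 0.04.
- Irreversible NEDA loss, m = 4. With records at months 7, 24, 48 and 72, and visit indicators standing in for random visit effects, rejection was 0.18 to 0.22 across runs. With four records of equal hazard and a fitted time-point random intercept it was 0.24. With m = 6 it was 0.28 to 0.36.
- On the irreversible-loss data, patient-clustered standard errors and a discrete-time model to first loss each brought rejection back to about 0.05 to 0.06.

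The excess therefore comes from leaving out the patient.

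**The case against.** The strongest defence is that the sentence is condensed wording. It follows directly from the remark about repeated measurements of the same individual, and its stated purpose is to handle within-subject correlation. It could mean time effects nested within patient, which would model that correlation. This is a journal article, and a full analysis plan may name the grouping unit. That stands as a possibility. It does not remove the point, because the article does fix the random-effects term and a programmer who followed it literally would fit the wrong model.

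Second, *End Points* defines one status per patient at 6 years. If that is the dependent variable, the outcome has no within-patient correlation and the inflation above does not arise. This stands too, but a model justified by repeated measurements does not fit a single status, so the text has to say which is meant.

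Third, the size rests on an unstated number of records and an unstated correlation. At ICC 0.1 with four records the error is only 0.086. The figures of about one in three need six records, whereas *End Points* names fewer fixed evaluations. This stands, and it is why the result is given as a range.

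Fourth, only predictors fixed at baseline were examined. The plan also has repeatedly measured biomarkers and lagged covariates, and inflation for those has not been shown.

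**Conclusion.** The random-effects specification is wrong as written or, at best, misworded. Read literally, with NEDA status stacked over visits, nominal 5% tests of baseline EDSS, MRI and relapse rate have a true type I error of about 0.09 to 0.36 (ICC 0.1 to 0.7, 4 to 6 records). For four records of irreversible NEDA the figure is about 0.18 to 0.24. For the primary outcome, the low end of the wider range is unlikely, because NEDA measured from screening is strongly dependent over time by construction.

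A reader might infer more, and the article does not support it:
- That the analysis will certainly ignore within-patient correlation. The stated aim is to account for it, and the nested reading remains open.
- That the efficacy result is compromised. The 6-year proportion does not need this model; only the predictor associations are exposed.
- That every biomarker P value is invalid. This was shown only for predictors constant within patient.
- That a random effect for the 9 clinics, or a Kaplan-Meier analysis to handle dropout, is required. The word clustering is left undefined, but no site inflation was shown. *T Cells, B Cells, and Natural Killer Cells Panel* already provides a common antibody cocktail and concordance checks, and *Missing Data* covers dropout separately.

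**What to change.** In *Association Modeling*:

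1. Name the patient as the grouping unit: a random intercept per patient, with a random time slope if the data support it, or patient-clustered standard errors. Enter time as a fixed effect. Apply the same to the repeatedly measured secondary outcomes.
2. State whether the NEDA dependent variable is the single 6-year status or repeated status. For the single status, ordinary logistic regression is enough.
3. If it is repeated and measured from screening, do not count records after first loss as new information. Use patient-clustered errors or a discrete-time model to first loss. The patient random intercept was checked above only for an outcome that can recover.

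The cost is wording and model code, with no new data. Confidence intervals for baseline predictors become wider than under the literal model, by a factor of √1.3 ≈ 1.14 to √4.5 ≈ 2.12 over the range in Step 1, so some associations will look less favourable.

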**Inclusion criteria**
Participants must be eligible for and already intend to commence cladribine tablets in accordance with the Australian Product Information (PI). Cladribine tablets are indicated for relapsing remitting patients with multiple sclerosis who do not have HIV infection, active chronic infection, are immunocompromised, have severe renal impairment, or are pregnant or breastfeeding.Participants must have the ability to understand the purpose and risks of the study, as outlined in the patient informed consent form and provide signed and informed consent and authorization to use protected health information in accordance with national and local privacy regulations.The participants must meet the McDonald criteria [43] for the diagnosis of relapsing remitting multiple sclerosis.Male or female participants aged 18-70 years.Be able to provide details for or consent to provide access to a stored minimum data set (ie, demographics, date of diagnosis, relapse information, and baseline expanded disability status scale score).Be able and willing to comply with all study procedures, including magnetic resonance imaging scanning, as per the protocol.Must agree to use contraception from baseline until 6 months after the last dose of cladribine tablets, unless they or their partners are infertile or surgically sterile.Participants must be aware of all precautions listed in the PI for Mavenclad, and any subsequent disease-modifying therapy treatment received within this clinical study must be adhered to.

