### Assessments

#### NEDA Status

NEDA-3 and NEDA-4 status (absence of clinical relapses, confirmed disability worsening, and new T2 lesions, including brain atrophy [NEDA-4 only]) will be assessed based on the clinical data uploaded into the database (MSBase) [44]. For this study, we will use the NEDA-4 criteria as defined by Kappos [16]. Physical examinations, vital sign assessments, and expanded disability status scale (EDSS) assessments will be performed throughout the study. Concomitant medications and adverse events are assessed at every study visit. On the basis of clinical and MRI parameters, patients with MS will be classified as NEDA-positive (responders) or NEDA-negative (nonresponders).

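### Baseline EDSS is tested as a predictor of NEDA 3, while confirmed worsening appears to be scored from the same EDSS reading, so that association can be distorted by an amount the documents do not let us fix

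*Protocol article*

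**What the plan says.** The Association Modeling section of the protocol article sets the dependent variable: "Our primary outcome is treatment response status according to NEDA 3". The purpose of the modelling is "to determine whether any clinical parameters are associated with outcome", and "Clinical factors included in the primary analysis will be EDSS, MRI, and relapse rate measures regressed at baseline". Age, sex and disease duration are named separately as confounders, so baseline EDSS reads as a tested factor and not only as an adjustment.

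The NEDA Status section defines the outcome through "absence of clinical relapses, confirmed disability worsening, and new T2 lesions". It says that "expanded disability status scale (EDSS) assessments will be performed throughout the study" and names no other disability scale. The End Points section defines the primary end point as "the proportion of patients with MS achieving NEDA status (responders) at 6-years relative to screening". The inclusion criteria list a minimum data set of "demographics, date of diagnosis, relapse information, and baseline expanded disability status scale score", which holds one baseline EDSS score.

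The visit list under End Points and Outcomes starts at baseline, before the first dose. The same paragraph then schedules the laboratory samples at screening. The two words appear to name one visit.

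**The concern.** If one starting EDSS reading is both predictor and reference, it sits on both sides of the model. A patient read too low by chance gets a low predictor value and a reference that later readings easily exceed. A patient read too high gets the reverse. Under a fixed worsening step, this makes low baseline EDSS look like a cause of failure and high baseline EDSS look like a marker of good response. A step size that depends on starting EDSS would add a second link between predictor and outcome through the definition itself.

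The study wants predictors of response to inform treatment decisions. A baseline EDSS coefficient that partly reflects how the outcome is scored could be reported as a clinical predictor of response to cladribine.

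**Working it through.** **The plan's own figures.** 150 × (1 − 0.20) = 120 patients with longitudinal data, and 120 × 0.50 = 60 nonresponders. Both match the Sample Size Calculation section. The check below uses n = 120.

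**What the documents do not give.** They give no EDSS reading-error SD, worsening step, confirmation interval or EDSS distribution. Everything about EDSS below is therefore an assumption.

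**Method.** Trials were simulated in which true baseline EDSS has no effect on relapse, MRI activity or real worsening. Scores are rounded to 0.5. There are 72 / 6 = 12 follow-up readings. Worsening means at least 1.0 point above reference at two consecutive visits. Failure means worsening or other failure (relapse or MRI). Failure or response is regressed on the baseline reading by logistic regression, a stand-in for the planned mixed model. A valid test rejects in about 5% of trials.

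- Set A: true EDSS mean 3, SD 1.5; 20% real worsening; 40% other failure. Failure before any false worsening is 1 − 0.80 × 0.60 = 52%, close to the planned 50%.
- Set B: true EDSS mean 2.8, SD 1.5; 20% real worsening; 35% other failure. Failure is 1 − 0.80 × 0.65 = 48%. There were 2000 trials per setting, so the simulation error on a 5% rate is √(0.05 × 0.95 / 2000) ≈ 0.5 percentage points.

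**Fixed 1-point step, same reading as predictor and reference**

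| Error SD | Set A rejection | Set B rejection | Set B odds ratio for response per EDSS point |
|---|---|---|---|
| 0 | – | 3.8% | 1.00 |
| 0.25 | about 5% | 5.2% | 1.01 |
| 0.35 | – | 6.7% | 1.05 |
| 0.4 | about 10% | – | – |
| 0.5 | about 17% | 15.2% | 1.13 |
| 0.7 | – | 37.8% | 1.23 |

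Repeated runs of Set A agreed within about one percentage point. Its odds ratio for failure at SD 0.5 was 0.88, and 1 / 0.88 = 1.14 for response, in line with Set B.

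**Is the shared reading the cause?** With a separate reference reading and the same fixed step, Set B returns to 4.5-5.6% at every error SD from 0 to 0.7.

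**More failures from the other components.** With 70% other failure in Set A, failure before any false worsening is 1 − 0.80 × 0.30 = 76%. Rejection is then about 5-9% across error SD 0.25 to 0.5. Relapse and T2 failures are not scored from EDSS and dilute the coupling.

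**A stepped rule (assumed steps of 1.5 / 1.0 / 0.5 as starting EDSS rises).** High starting EDSS now makes failure easier, while the shared reading makes it harder, so the two links pull in opposite directions. With the same reading for both roles, Set A gives about 5-6%. In Set B the offset is only partial: 4.8% at SD 0.25, 5.6% at 0.35, 8.1% at 0.5 and 20.6% at 0.7. With a separate reading under this rule, the second link stands alone and Set A gives 9-12%.

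**Relapse or MRI failure only.** With the disability component left out of the outcome, rejection for baseline EDSS stayed near 5% in every setting. That is expected, since no EDSS reading then enters the outcome.

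**The case against.** The strongest objection is that the premise is inferred. No sentence says that worsening is counted from the EDSS reading used as predictor. The article uses both screening and baseline, and leaves the reference value, step and confirmation rule to the full protocol or analysis plan, as articles commonly do. This stands as a limit: the shared reading is the natural inference from the text, not a stated fact, and the absence of those details is not itself a finding. The point remains because the article does fix the outcome, its reference time and the tested predictor, and nothing shown separates them.

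A reader might infer that reading error alone creates an association, or that the EDSS test is invalid. The figures do not support either. Inflation is negligible at error SD 0.25 and small at 0.35. The documents report NEDA 3 of 44% (Introduction) or 47% (Discussion) at two years, so 53-56% had already failed by then. Six-year failure through relapse or MRI could well exceed 40%, which moves the result towards the 5-9% range. A stepped rule shrinks it too.

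A reader might also infer that the primary end point is biased. It is not: the proportion with NEDA does not involve baseline EDSS as a predictor. The individually modelled biomarkers are not scored from EDSS either.

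Taking the predictor from a separate EDSS examination looks like an obvious remedy. It works under a fixed step, but not under a stepped one, and the minimum data set lists no second pre-treatment EDSS.

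On the other side, the plan's false discovery rate adjustment and cross-validation do not remove the problem. The first addresses multiplicity, and in the second every fold carries the same coupling.

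**Conclusion.** The point holds in a conditional form. The article tests baseline EDSS against an outcome whose disability component appears to be scored from that same EDSS, so the association can be created or distorted by the scoring. The plausible size runs from no visible inflation to about 17% rejection at a nominal 5%, for error SD up to 0.5. Only the larger assumed error of 0.7 gives more (37.8% with a fixed step). These figures rest on assumed reading error, EDSS distribution, worsening rule and failure mix, and on a logistic model of final status. The documents cannot narrow the range. The effect is confined to the baseline EDSS coefficient and, to a lesser degree, to factors correlated with it: with an age covariate assumed to correlate 0.5 with true EDSS, the age test rejected in 10% of trials at SD 0.5. This is a cheap improvement to the association analysis, not a defect in the primary estimate.

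**What to change.** In Association Modeling, add that baseline EDSS will also be tested against NEDA failure by relapse or new MRI lesion only, and that any claim that EDSS predicts response will rest on that model. Keep baseline EDSS in the full NEDA 3 model as an adjustment covariate, and state that its coefficient is not interpreted as a predictor. This works whichever reference reading and worsening step the full protocol uses, provided relapse is not itself scored from EDSS change; the article gives no such definition.

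The cost is a sentence or two in the analysis plan and one extra model on data already being collected. The downside is that the EDSS test leaves out the disability component, so it cannot say whether baseline EDSS predicts worsening. Some distortion of correlated covariates can remain in the full model, and comparing their coefficients with those in the two-component model would show whether it matters.

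### The elastic net is run on the full factor set with no rule keeping out follow-up measures that define NEDA, and it is wrongly described as free of the multiple-testing problem

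*Protocol article*

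**What the plan says.** All references are to the protocol article.

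- **Input to the elastic net** (Association Modeling): "This will be performed on the entire factor set using the GLMNet package in the R program". The aim is a multi-biomarker signature of treatment response, and the primary outcome is NEDA 3 status. The End Points section sets this at 6 years relative to screening.
- **What counts as a factor** (Sample Size Calculation): 120 patients are expected to have "longitudinal data for all measured factors: clinical, cellular, and omics".
- **Timing of clinical factors** (Association Modeling): "Clinical factors included in the primary analysis will be EDSS, MRI, and relapse rate measures regressed at baseline". This sentence belongs to the mixed models. No such limit is given for the elastic net, and the same paragraph allows covariates to be defined as lagged or leading.
- **What defines the outcome** (NEDA Status): relapse, confirmed disability worsening and new T2 lesions, with brain atrophy added for NEDA-4.
- **Samples tied to events**: End Points and Outcomes places the Tv sample at exacerbation, or before a treatment change or redosing. Study Design makes relapse or new MRI activity the indication for redosing.
- **Safeguard**: the elastic net is to run inside cross-validation to prevent overfitting.
- **Multiplicity**: "This complementary approach is not susceptible to multiple testing burdens".
- **Purpose** (Sample Size Calculation): "To detect more minor differences, we will use a penalized regression analysis within a machine learning framework using the GLMNet tool".

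**The concern.** NEDA at 6 years accumulates from screening to month 72, so every follow-up relapse, EDSS or MRI value lies inside the outcome window. A model given those values reconstructs the outcome rather than predicting it.

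Leaving out the clinical components alone would not be enough. A Tv sample often exists because disease activity occurred. Lymphocyte subsets at months 48 to 72 can reflect redosing that was itself triggered by nonresponse, and the section on lymphocytes as biomarkers says cladribine markedly reduces B cells. Such values can be consequences of losing NEDA and still be read as predictors of it.

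The second issue is the sentence on multiple testing. It tells the reader that a selected panel needs no allowance for how many candidates were searched. The Introduction wants biomarkers for the choice between redosing and changing therapy, so a circular panel, or one made of noise, could reach that use.

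**Working it through.** **1. The plan's own counts.** The plan states "This is a longitudinal study of 150 patients with MS entering the study and predicted to have no more than 20% dropout". Then 150 × (1 − 0.20) = 120, and 50% of 120 = 60, which agrees with "With 120 cases (60 responders vs 60 nonresponders". The counts reproduce, and the simulations below use n=120. The stated "80% power to detect a minimum mean biomarker difference of 10% at a Benjamini-Hochberg false discovery rate of 0.05" can be neither confirmed nor refuted, because no SD, number of tests or share of true signals is given. The point does not depend on it.

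**2. Passages side by side.** The named clinical factors (EDSS, MRI, relapse rate) measure the same domains as the NEDA components. The baseline limit is attached to the primary mixed models. The elastic-net sentence has neither a time limit nor an exclusion.

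**3. Can cross-validation detect circular predictors?** Assumptions: three independent components, each occurring with probability q, and nonresponse if any occurs. For 50% nonresponse, q = 1 − 0.5^(1/3) = 0.206.

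A single component used as predictor has specificity 1, because no responder has it. Its sensitivity is 0.206 / 0.5 = 0.413. So AUC = (1 + 0.413) / 2 = 0.71. All three components together give AUC 1 by definition.

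The simulation used a logistic elastic net, mixing parameter 0.5, 200 noise predictors, 5-fold cross-validation, the penalty at minimum deviance, and 15 data sets.

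| Predictors | Mean cross-validated AUC |
|---|---|
| Noise only | 0.48 |
| Noise + 3 weak stand-ins for baseline covariates | 0.51 |
| Noise + 1 follow-up component | 0.71 |
| Noise + 3 follow-up components | 1.00 |

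The stand-ins were each component plus normal noise of SD 2. Cross-validation passes the circular predictors because they are present in every fold. Weakly related covariates do not produce the effect.

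**4. Is the method free of the multiple-testing problem?** Null simulation: 60 versus 60, no predictor related to outcome, mixing 0.5, 10-fold cross-validation, penalty at minimum deviance, 40 data sets per setting. The article does not state the number of predictors; 50 and 500 are assumed.

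| Predictors | At least one marker selected | Apparent AUC when any selected | Best cross-validated AUC over the penalty path |
|---|---|---|---|
| 50 | 53% (21/40) | 0.75 | 0.56 |
| 500 | 55% (22/40) | 0.87 | 0.56 |

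The true AUC is 0.50. The simulation standard error of the selection rate is √(0.525 × 0.475 / 40) = 0.08, so the rate should be read as about half. A panel made only of noise is therefore a common result.

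**5. How much optimism remains?** The cross-validated figure exceeds 0.50 by about 0.06, even when the best penalty is picked on the same data. The apparent fit exceeds it by 0.25 to 0.37. If the 20 strongest markers were first chosen on all the data, cross-validated AUC in the 500-predictor null setting was 0.85. The article does not say it will filter this way, but the result shows why any filtering must sit inside the folds.

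**The case against.** The strongest reply is that the circularity is inferred. No sentence says that follow-up relapses, EDSS worsening or new lesions enter the elastic net. The phrase about all measured factors comes from a sentence on how many patients will have data, not from a definition of model inputs. The stated aim is a biomarker signature, and where EDSS, MRI and relapse rate are named they are baseline values, which are legitimate predictors. The lagged or leading wording shows that timing was considered, and the full protocol or SAP may define the set. This stands as far as it goes: a reader might infer that the model contains its own outcome, and the article does not support that. What remains is that the only stated rule is the whole set, without exclusion, and that the baseline limit is written for a different analysis.

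Second, cross-validation is planned. A reader might infer from the apparent AUCs of 0.75 and 0.87 that the reported accuracy must be inflated. That does not follow, because the article does not say it will report apparent fit, and the cross-validated figure under the null is about 0.56. The objection stands for optimism, but not for circular predictors.

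Third, a reader might infer that the claim of added power for multi-marker signatures is false. Null simulations cannot test power, and joint modelling can pick up combined weak signals that single-marker screening misses. That claim is left alone here.

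Fourth, the elastic net is a complementary discovery analysis, not the primary one. That limits the harm but does not make the multiplicity sentence correct.

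**Conclusion.** The point holds in two parts.

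- **Predictor timing.** As written, the elastic net has no barrier against outcome components, event-triggered samples or post-redose biomarkers, and its cross-validation would not reveal them. The possible size is large: cross-validated AUC of 0.71 to 1.00 with no biomarker signal. It is conditional on such values actually entering, which the article leaves open.
- **Multiplicity.** The statement is wrong regardless of any fuller document, since about half of null data sets yielded a panel. The effect on reported accuracy is modest (about 0.06 in AUC) if all selection is inside the folds and the out-of-fold figure is reported.

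The figures rest on independent components, a mixing parameter of 0.5, 50 to 500 predictors and small numbers of simulated data sets. An epigenome-wide array would supply far more predictors than were tried.

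**What to change.** 1. At each planned analysis point (for example baseline and months 7, 24 and 48), admit only predictors measured up to that point and predict loss of NEDA after it among patients still event-free.
2. Exclude NEDA components and samples from the outcome window, including Tv and post-redose samples. Keep baseline EDSS, MRI and relapse history. The Tv-versus-stable comparison in End Points can remain as a separate analysis. A month-7-only rule is not needed and would discard later biomarkers that the plan means to use.
3. Put all filtering, scaling and tuning inside nested cross-validation. Report out-of-fold AUC with a confidence interval and a permutation P value.
4. Delete the multiple-testing statement.

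No new data are needed, and the study is expected to conclude in 2027. The cost is some analysis code, changed wording and lower reported accuracy. Later analysis points will also hold fewer event-free patients: at the 2-year NEDA 3 rates the article cites (44% and 47%), 120 × 0.44 = 53 to 120 × 0.47 = 56 at month 24. At month 48 the last scheduled sNfL value is from month 36 and the last scheduled methylation value from month 24.
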